### Ethics and dissemination

2.12

Before this study, permission was first obtained from Ethics Board of University Hospital Center Zagreb, Zagreb, Croatia (Number 02/21 AG), and Ethics Committee of Faculty of Medicine, University of Rijeka, Rijeka, Croatia (Number 217 0-24-04-3-19-3). Written informed consent will be obtained from each patient before enrollment by independent physician. Any modifications to the protocol which may impact on the conduct of the study, potential benefit of the patient or may affect patient safety, including changes of study objectives, study design, patient population, sample sizes, study procedures, or significant administrative aspects will require a formal amendment to the protocol. Such amendment will be approved by the aforementioned Ethics Committees and communicated through clinicaltrial.gov before implementation. Results of this trial will be submitted for publication in peer-reviewed journal and for presentation at scientific conference.

## Statistical analysis plan

3

The analysis will be conducted by Statistical Package for the Social Sciences (SPSS) Statistics software, version 25.0 (IBM Corporation, Armonk, NY). Continuous and ordinal data will be presented as the median and interquartile range (IQR), while categorical data will be presented as raw numbers and as frequencies. Distribution of data will be tested by the Kolmogorov-Smirnov and Shapiro-Wilk tests. Non-parametric tests like Friedman's 2-way ANOVA with post-hoc Dunn test and Mann–Whitney *U* test will be used to assess pair-wise differences between related and independent variables with non-normal distribution. Data with normal distribution will be analyzed by Student *t* test. Correlations will be analyzed with Spearman test. For sensitivity-specificity measurements, the receiver operator characteristics (ROC) curve estimation will be used. Values of *P* < .05 is considered significant. An interim-analysis is performed on the primary endpoint when 50% of patients have been randomized. The interim-analysis is performed by an independent statistician, blinded for the treatment allocation.

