### Randomization

2.4

Patients who meet the criteria will be randomly allocated to the lidocaine group or to the control group. Randomization will be computer generated with allocation ratio 1:1. Randomization and enrollment will be done by an independent physician who is not directly involved in the care of the patients. Anesthesiologist will not be blinded to the grouping, but the participants. Unblinding could be done in case of any medical emergency. In case of unblinding, the patient will be excluded from the trial. Allocation concealment will be ensured with closed envelop method, which cannot be opened until induction of the anesthesia have been completed

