### Interventions

2.5

Patients included in the trial will be randomly assigned to the lidocaine group (Group L) or to the control group (Group C). Patients in Group L, following general anesthesia induction, will receive topical anesthesia of the throat before endotracheal intubation with 40 mg of lidocaine and also regional anesthesia of the scalp with 2% lidocaine in maximum dosage 4 mg/kg before Mayfield frame placement. Total dosage of lidocaine will be up to 400 mg. Regional anesthesia of the scalp will be performed using technique described in relevant literature.^[16]^ Patients in Group C will have general anesthesia only without any lidocaine administration. All patients will undergo craniotomy and cerebral aneurysm clipping surgery with preoperative placement of lumbar CSF drainage, when it is otherwise indicated neurosurgically.

Blood samples will be taken from every patient included in the study at four timepoints: before induction of the anesthesia (baseline), at the time of incision, at the end of surgery and 24 hours from start of anesthesia. CSF samples will be taken from lumbar CSF drainage system at 2 timepoints: at the time of incision and at the end of surgery. Concentrations of IL-1β, IL-6, and TNF-α in plasma and CSF will be measured using enzyme-linked immunosorbent assay (ELISA) specific for each cytokine, according to manufacturer instructions.

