### Sample size calculation

2.9

Based on previous studies, we performed a sample size estimation before recruitment with the power analysis module of STATISTICA software version 10.0 (StatSoft Inc., San Diego, CA), using α = 0.05 and β = 0.1.^[17,18]^ We determined that a minimum of 20 participants was required per group for pair-wise comparisons of our samples.

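### The plasma baseline collected in every patient is not used in the between-group comparison, which may cost power (plasma only; the planned tests remain valid)

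*Protocol article*

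**What the plan says.** Section 2.5 (Interventions) of the protocol article states: "Blood samples will be taken from every patient included in the study at four timepoints". The first, before induction, is labelled baseline. The others are at incision, at the end of surgery and 24 hours from the start of anaesthesia. CSF is sampled only at incision and at the end of surgery, both after lidocaine has been given in Group L.

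Section 2.7 (Primary outcome) names the concentrations of three cytokines in plasma and CSF. It does not define them as changes or as baseline-adjusted values.

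Section 3 (Statistical analysis plan) tests the distribution and then chooses the method. For non-normal data, Friedman with post-hoc Dunn and Mann–Whitney "will be used to assess pair-wise differences between related and independent variables with non-normal distribution". Otherwise, "Data with normal distribution will be analyzed by Student" *t* test. Spearman correlations and ROC curves are also listed. No ANCOVA, change from baseline, mixed model or group-by-time term appears.

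Section 2.9 (Sample size calculation) sets the size "using α = 0.05 and β = 0.1" and concludes that "a minimum of 20 participants was required per group for pair-wise comparisons of our samples".

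**The concern.** The hypothesis is that lidocaine lowers cytokine levels. With 1:1 randomisation against a no-lidocaine control, that is a contrast between groups. The named tests that make this contrast, Mann–Whitney and Student *t*, take no covariate, so differences between patients that existed before treatment stay in the error term. The one listed method that could take in the baseline, Friedman/Dunn on related samples, compares timepoints and gives no estimate of the difference between lidocaine and control.

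If a patient's baseline predicts later values, the trial pays for a measurement and then leaves it out of the comparison it could sharpen. With a planned minimum of 20 per group, precision is scarce. Choosing the test by a normality check adds a smaller problem: cytokines and timepoints may be analysed by different tests, so results need not share an effect scale.

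**Working it through.** **Inputs.** From the article: 20 per group, allocation 1:1, α = 0.05, β = 0.1 (power 90%). Not given: sidedness (two-sided assumed), effect size, SD, and the correlation r between baseline and follow-up. The article says only "Based on previous studies, we performed a sample size estimation before recruitment". I therefore show r from 0 to 0.7 and two standardised differences d.

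**Step 1: the plan's own figure.** Without an effect size or SD, 20 per group can only be solved backwards. Normal approximation: d = (1.960 + 1.282) × √(2/20) = 1.03. With the noncentral *t* distribution on 38 df, 90% power needs d = 1.05 (0.94 if one-sided). I use 1.05 as the implied difference and 0.8 as an assumed smaller one.

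**Step 2: unadjusted power.** Noncentrality = d × √(n/2) = d × √10.
- d = 0.8: 0.8 × 3.162 = 2.530, power 69%.
- d = 1.05: about 3.33, power 90%.

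**Step 3: ANCOVA power.** Adjustment multiplies the residual variance by 1 − r². Estimating the covariate slope costs one degree of freedom (37 df) and a factor of about 1 + 1/36. So f = (1 − r²)(1 + 1/36), and the noncentrality is d√10/√f.

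| r | f | Noncentrality, d = 0.8 | Power, d = 0.8 | Power, d = 1.05 |
|---|---|---|---|---|
| unadjusted | 1 | 2.530 | 69% | 90% |
| 0 | 1.028 | 2.495 | 68% | 89% |
| 0.3 | 0.935 | 2.616 | 72% | 92% |
| 0.5 | 0.771 | 2.881 | 80% | 96% |
| 0.7 | 0.524 | 3.494 | 93% | 99% |

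Break-even is near r = 0.17, where f = (1 − 0.0289) × 1.0278 = 0.998.

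**Step 4: simulation check.** With 6,000 trials per setting, 20 per arm and data normal on the analysis scale (as log concentrations would be if log-normal), power at d = 0.8 was 66–68% for Mann–Whitney and 68–70% for the *t* test. For ANCOVA it was 67%, 72%, 79% and 93% at r = 0, 0.3, 0.5 and 0.7. With no effect, all three methods rejected in about 5% of trials.

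**Step 5: can tests over time within an arm stand in for the contrast?** Suppose there is no lidocaine effect and both arms share the same true change. If each arm's paired test has power p, exactly one arm is significant with probability 2p(1 − p), which cannot exceed 50%. For a paired *t* test with 20 patients and r = 0.5:

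| Shared change | Exactly one arm significant |
|---|---|
| 0.4 SD | 48% |
| 0.6 SD | 40% |
| 0.8 SD | 14% |
| 1.0 SD | 2% |

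This is a simplified stand-in for Friedman/Dunn over four timepoints. It shows why such results cannot carry the conclusion. It does not estimate an error rate of this plan.

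**The case against.** The strongest reply is that nothing in the plan is invalid. Mann–Whitney and Student *t* compare the groups directly, match the primary outcome as defined, and keep their type I error under randomisation. That stands, and it makes this a point about efficiency.

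The gain also rests on an unknown correlation. The exclusion criteria (acute infection, immunological disease, steroid treatment) narrow baseline variation, and if later levels mainly reflect the response to surgery, r could be low. That stands too: the benefit is 2 to 3 points at r = 0.3, and there is a loss of about 1 point at r = 0.

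A reader might go further and infer that the baseline is not used at all, or that the authors will claim efficacy because Group L changes significantly and Group C does not. The article supports neither. The baseline can enter the related-sample analysis as a timepoint, and no sentence says that conclusions will be drawn from separate within-arm results. Describing the time course in each arm is legitimate. The high percentages in Step 5 also occur only for modest shared changes and fall quickly as the change grows.

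Finally, section 3 is a condensed text, its non-parametric tests are introduced as examples, and a fuller plan may name covariates. But the section does state the tests and the rule for choosing between them, so the point concerns a stated choice and not a missing detail.

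**Conclusion.** The point holds for plasma, as an avoidable loss of efficiency in a valid analysis. At 20 per group and two-sided 0.05, adjustment for the baseline changes power by −1, +3, +11 and +23 to +24 points at d = 0.8 for r = 0, 0.3, 0.5 and 0.7. At d = 1.05 the changes are −1, +2, +6 and +9 points. The gain is therefore material only if r is about 0.5 or more. These figures assume a two-sided test, approximate normality on the log scale and a linear relation with baseline. Neither r nor d can be checked from the article.

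The point does not extend to own-baseline adjustment in CSF, where no pre-treatment sample exists. Nor does it show bias or an inflated type I error in the planned between-group tests.

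**What to change.** - **Plasma:** make the between-group analysis an ANCOVA at each post-baseline timepoint, or a mixed model with group, time and group-by-time. Use log concentration as the outcome and the patient's log plasma baseline as covariate. Report the ratio of Group L to Group C with its 95% CI, and keep Mann–Whitney as a sensitivity analysis. Fixing the model in advance also removes the choice of test by a normality check.
- **CSF:** keep an unadjusted between-group comparison. Baseline plasma concentration is an optional covariate.
- **Interpretation:** state that conclusions rest on the between-group contrast and that Friedman/Dunn results are descriptive.

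The cost is revised wording and a standard SPSS procedure; no new data are needed. The downside is about 1 point of power if the correlation is near zero, and reliance on a log-scale model.

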### Primary outcome

2.7

The primary outcome are concentrations of IL-1β, IL-6, and TNF-α in plasma and CSF of patients undergoing craniotomy for cerebral aneurysm surgery under general anesthesia. These cytokines will be measured at specific timepoints, as described.

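### The test is chosen by a normality check, and the normal branch names only Student's t test, which provides no method for four related plasma samples

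*Protocol article*

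**What the plan says.** All the analysis rules stand in section 3 of the protocol article, Statistical analysis plan.

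- Choice of branch: "Distribution of data will be tested by the Kolmogorov-Smirnov and Shapiro-Wilk tests". No rule is given for when the two tests disagree, or for when timepoints or arms give different answers.
- Non-normal branch: "Friedman's 2-way ANOVA with post-hoc Dunn test and Mann–Whitney" U tests "will be used to assess pair-wise differences between related and independent variables with non-normal distribution".
- Normal branch: "Data with normal distribution will be analyzed by Student" t test. Nothing else is named, and whether the test is paired is not stated.
- Threshold: P < .05 "is considered significant". No adjustment for multiple comparisons is stated in either branch.
- Summaries: medians with interquartile ranges for all continuous data, whichever branch applies.

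The data structure comes from section 2.5, Interventions: "Blood samples will be taken from every patient included in the study at four timepoints", while "CSF samples will be taken from lumbar CSF drainage system at 2 timepoints". Section 2.7 makes all of these measurements primary: "The primary outcome are concentrations of IL-1β, IL-6, and TNF-α in plasma and CSF". Section 2.9 gives at least 20 participants per group.

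**The concern.** The two branches are not parallel. The non-normal branch recognises that repeated samples from one patient are related, and it supplies an omnibus test followed by a post-hoc procedure. The normal branch supplies a two-sample tool for a four-sample problem. Within-arm change in a plasma cytokine can be put through a t test only by splitting it into pairs, and the only stated rule for those pairs is P < .05.

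The same finding, that a cytokine changed during surgery, would then carry a false-positive rate that depends on the branch its data fell into. With 20 patients per arm, normality tests are a weak and unstable guide, so cytokines and timepoints in one trial could be judged on different footings. Because two normality tests are named without a rule for disagreement, the branch can also be settled after the results are seen. A t-test P value about means would moreover stand beside medians in the tables.

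**Working it through.** **No plan figure to reproduce.** The protocol states no error rate for these comparisons. Its one related number, 20 per group, comes without an effect size or SD, so it is used here only as the sample size.

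**Step 1: number of comparisons.** Four plasma times (section 2.5) give C(4,2) = 4 × 3 / 2 = 6 pairs per cytokine per arm. With three cytokines that is 6 × 3 = 18 per arm, and 18 × 2 = 36 over both arms. Against baseline only, there are 3 contrasts per cytokine per arm. CSF has two times, so C(2,2) = 1 pair, for which one paired t test is enough.

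**Step 2: family-wise error in the t branch.** If the six tests were independent, the error would be 1 − (1 − 0.05)^6 = 1 − 0.735 = 26.5%. They share data, so this is too high. For four equally correlated normal means with known variance, the tail of the studentized range at 1.96 × √2 gives 20.3%. Simulation with n = 20, normal data and no time effect gives:

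| Procedure within one arm, one cytokine | At least one false positive |
|---|---|
| Six paired t tests, each at 0.05 | about 20–22% |
| Three paired t tests against baseline, each at 0.05 | about 12–13% |
| Six paired t tests, Bonferroni 0.05/6 = 0.0083 | about 4% |
| Friedman, then Dunn with Bonferroni | about 3–4% |
| Friedman, then Dunn without correction | about 5% |

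Within-patient correlations are assumed. Values of 0.3 to 0.7 were used for the baseline contrasts and the Friedman rows, and 0 to 0.8 (equal or decaying with time) for the six-test rows. The results hardly depend on them. In the last row the 5% is supplied by the Friedman test acting as a gate, so that figure holds when nothing changes at any time.

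**Step 3: how unstable is the choice of branch?** For right-skewed (lognormal) values with log SD 0.3 to 0.6, which is an assumption, and n = 20 per arm, Shapiro-Wilk and Kolmogorov-Smirnov (Lilliefors form) point to different branches in about 20–27% of two-arm comparisons. A lognormal sample of 20 passes Shapiro-Wilk in about 75% of cases at log SD 0.3, falling to about 7% at log SD 1.0.

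**Step 4: how often does the t branch do harm?** Assume it is used only when all four raw samples pass Shapiro-Wilk, with correlation 0.3 to 0.7 and no time effect:

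| Log SD (assumed) | t branch entered | Entered, and at least one of six tests false positive |
|---|---|---|
| 0.3 | 33–43% | 8–9% |
| 0.4 | 15–24% | 4–6% |
| 0.5 | 6–11% | 1.5–2.7% |
| 0.6 | 1–5% | 0.5–1.3% |

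**Step 5: between-arm comparison.** Pretesting and then choosing t or Mann–Whitney gives a type I error of 5.2–5.6%, or 5.6–5.8% if the smaller P is taken whenever the normality tests disagree.

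**The case against.** A reader might infer that the plan will compare the four plasma samples by six uncorrected t tests. The text does not go that far. It does not say that the t test is paired, that all pairs are tested or that results stay unadjusted, and three baseline contrasts fit the wording equally well. This objection stands: six is a maximum and 21% is an upper case. With three contrasts the rate is still about 13%.

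A reader might also infer that the trial's main conclusion carries a 21% error rate. It does not. The hypothesis is between arms, where Student's t is the ordinary counterpart of Mann–Whitney U and the inflation is negligible (step 5).

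The 21% also applies only once the t branch is entered. With skewed data that may be uncommon (step 4), and the choice of medians for all summaries suggests that the authors expect the rank route. That stands too, although the log SDs and the branching rule behind step 4 are assumptions.

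It can be said that crediting Dunn with a correction which the plan does not state is uneven. That is fair, but it does not close the gap, since Friedman followed by uncorrected Dunn still gives about 5% under no change.

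Lastly, a condensed article may leave a tie-break rule, a parametric repeated-measures method or an adjustment to a fuller plan, and the list of non-parametric tests is worded as examples. Those omissions alone would be no finding. The normal-data sentence is different, because it assigns a test that does not fit the design. A fuller plan would have to replace it, not merely add detail.

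**Conclusion.** The point holds in limited form. The plan chooses its test by a data-driven normality check, and the normal branch names no method suited to four related samples. Where that branch is entered and there is no time effect, the chance of at least one false positive per cytokine per arm is about 21% with all six pairs or about 13% with three baseline contrasts, against about 4–5% under Friedman with Dunn. These figures rest on n = 20, normal data in the t branch, paired tests, a literal reading of P < .05 and assumed correlations that matter little.

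The scope is within-arm plasma change over time. CSF and the between-arm hypothesis are essentially unaffected. The wording should be corrected, but the point does not undermine the trial's central comparison.

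**What to change.** Delete the normality-test branch and prespecify one method for every cytokine and time. Either of these would do:

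- A mixed model on log concentrations with group, time and group-by-time terms and multiplicity-adjusted contrasts (for example Holm), reported as ratios with 95% confidence intervals. This also answers the between-arm question directly.
- Friedman with adjusted Dunn for all within-arm plasma comparisons and Mann–Whitney U for all between-arm comparisons, whatever the distribution looks like. The two CSF times need a single paired rank test. This option agrees with the medians already planned for the tables.

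The cost is a few lines of analysis text, with no new patients, samples or assays. The downside is fewer nominally significant time contrasts.

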## Discussion

4

Increasing data confirm benefit of local anesthetics in patients undergoing craniotomy. Lidocaine can diminish autonomic response to the placing of Mayfield's frame when administered as scalp block or local infiltration. Regional and intravenous administration of lidocaine can reduce postoperative pain. Another indication of local anesthetic use is to reduce autonomic nervous system response to direct laryngoscopy and endotracheal intubation.^[10]^

Recent studies suggest systemic anti-inflammatory effect of local anesthetics in craniotomy patients, but also acknowledge the need for further investigation.^[19,20]^ Lidocaine has proven anti-inflammatory local and systemic effect, even at low plasma concentrations.

Therefore, we propose a clinical trial to investigate effect of lidocaine administration on perioperative levels of pro-inflammatory cytokines, which might be crucial in pathology of cerebral aneurysms. Measuring concentrations of IL-1β, IL-6, and TNF-α in plasma and CSF might provide insight regarding the effect of lidocaine on local and systemic inflammatory response.

Furthermore, this trial will investigate potential impact of decreased inflammatory response on major neurological and infectious complications in early postoperative period, as well as on outcome of the treatment.

Trial will test the hypothesis that lidocaine administration decreases concentrations of IL-1β, IL-6, and TNF-α in plasma and CSF in patients undergoing cerebral aneurysm surgery. Results of the trial could provide insight into influence of lidocaine on local and systemic inflammatory response in cerebrovascular surgery, and might improve future anesthesia practice and treatment outcome.
